#### 9.3.2 Main Analysis for Aims 1 and 3a

##### Aim1:

First, we will perform a multivariate Hotelling *t*-test to simultaneously compare the baseline to follow-up change in the three primary outcomes between the arms to protect the type I error rate from multiplicity. If significant, subsequent analyses will be performed without further multiplicity adjustment. If not, subsequent comparisons will be performed with a conservative Bonferroni correction at the  $\alpha=0.05/4=0.0125$  level. This protected test approach has been recommended in the statistical literature(63) and used in other exercise intervention trials with multiple outcomes.(64)

Second, we will fit a series of linear mixed models(65) using the SAS® MIXED procedure with baseline to follow-up change in each of the continuous outcomes (LLFDI function/disability, walking ability, other measures of mobility performance) as the dependent variable; intervention arm (standard/*On the Move*), as the fixed effect of primary interest; baseline value of outcome as an additional fixed effect covariate; and a facility random effect to account for greater similarity of participants from the same facility compared to different facilities and resulting non-independence of observations within facility (ie. clustering). We will construct appropriate means contrasts to estimate difference in gains in the two interventions when delivered by exercise leaders (Aim 1) whose statistical significance of the estimates will serve as formal tests of hypotheses. We will consider adding other baseline measures found to be significantly

different between the arms or deemed important as additional fixed effect covariates in the model to assess robustness of the findings. We note that waiting of participants randomized to staff activity personnel classes constitute a group of control participants, if smaller, without any intervention. Therefore, we will perform another sensitivity analysis employing a similar analytic strategy but with three intervention arms (*On the Move*/Standard/Wait List Control).

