#### 6.2.1.1 Function and Disability

Late Life Function and Disability Instrument (LLFDI).(35, 36) Our primary function and disability outcome will be the LLFDI. The LLFDI is a pair of self-report measures targeted for assessing physical function and disability in older adults with acute or chronic problems, and designed to be more sensitive to change than similar measures. The two components of the LLFDI correspond to the activity (LLFDI – function) and participation (LLFDI – disability) components of the World health Organization’s International Classification of Function, Disability and Health model. The LLFDI function component has 32 items in three dimensions, basic lower extremity (BLE), advance lower extremity (ALE) and upper extremity (UE) and the LLFDI disability component has 16 items representing two dimensions, frequency of performance and limitation in performance of life tasks. We’ve selected the LLFDI because 1) it measures both function and disability which are critical components of independence, 2) it includes a wide variety of life tasks in various social areas thus extending beyond the traditional focus of just activities of daily living, 3) the scale was designed with sufficient breadth of items and increments of rating in order to minimize ceiling and floor effects and maximize the scale’s ability to detect change over time, and 4) it is a continuous outcome which gives us greater power than a dichotomous outcome to detect change over time. We will focus our analyses on the LLFDI function and disability dimension scores (i.e. BLE function, ALE function, UE function, disability frequency and disability limitation). We will also examine the disability domain scores (social role, personal role, instrumental role and management role) since they may provide insight into the impact of the disability on frequency of performance and perceived limitations.(36) The LLFDI function and disability scales have established known groups validity and the test-retest reliability is moderate to high for the disability component (ICCs range from 0.68 to 0.82) and extremely high for the function component (ICCs range from 0.91-0.98 for the dimensions). Scores range from 0-100; higher scores represent less difficulty and less disability.

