### 9.2 Sample Size

We base our sample size justification on prior data from our RESTORE and PRIME pilot studies, two-tailed tests conducted at the  $\alpha=0.05$  level, a conservative attrition rate of 10% between baseline and follow-up assessments, practical consideration of a class size of 10 participants for group exercise, computational techniques that match our study design and proposed analytical approach as much as possible within the constraints of already published methodologies and commercially available sample size and power software (PASS 2002®, Number Cruncher Statistical Systems, Inc., Kayesville, Utah), and ability to detect differences that correspond to published meaningful change criteria(57) or moderate Cohen's effect sizes of  $d=0.5$ .(58)

The numbers needed to enroll in order to detect statistical significance of intervention effect when delivered by an exercise leader (Aim 1), are presented in **Table 1**. We take into account the clustering of participants by facility by assuming an intracluster correlation of 0.1 and a resulting design effect of 1.90 to appropriately inflate the sample size accordingly.(59) In

summary, a total of 280 participants with 140 in each arm will allow us to detect statistical significance in intervention effects in all main outcomes with at least 80% statistical power.

**Table 1. Number needed to enroll for detecting effects of intervention incorporating clustered design (x1.90), attrition (10%), and rounded up to class size of 10.**

| Outcome                    | Prior Information                |                                 |                                         | Estimated Sample Size                                   |                                 |
|----------------------------|----------------------------------|---------------------------------|-----------------------------------------|---------------------------------------------------------|---------------------------------|
|                            | Baseline Standard Deviation (SD) | SD in Baseline-Follow up Change | Meaningful Difference Targeted (Source) | Completers Needed Per Arm assuming No Clustering | Number Needed to Enroll Per Arm |
| LLFDI Overall Function     | 6.15                             | 4.86                            | 3.08 ( $d=0.5$ )                        | 41                                                      | 90                              |

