### 9.3 Data Analyses

#### 9.3.1 Overview

All statistical analyses will be performed or overseen by [name] using SAS® version 9 (SAS Institute, Inc., Cary, North Carolina) and Salford Predictive Miner® (Salford Systems, Inc., San Diego, California) based on the **intention-to-treat** philosophy. We will begin by summarizing data by arm and time point as well as pre- to post-intervention change using appropriate descriptive statistics for continuous (mean, standard deviation, median, range) and categorical (frequencies, percentages) to elicit information about general data quality and their distributional characteristics. Next, we will perform the modeling and inferential analyses to address the main hypotheses. First, the baseline participant characteristics will be compared between the two arms (see Avoidance of Bias below). Although no significant differences are expected, any significant differences will be noted and accounted for as covariates in the main analyses. Second, main analyses to address Aims 1-3 will be performed as outlined below. If residuals reveal violations of linear models assumptions, we will Box-Cox transform(60) the response variables. The two-step protected test approach will be used to control the experimentwise type I error rate from multiple outcomes, and multiple imputation(61, 62) will be used to account for any missing data in the main analysis. Third, we will perform the exploratory analyses to address Aim 4, using a data mining philosophy. Finally, we will perform a set of exploratory analyses to potentially extend our findings and generate new hypotheses, as well as a set of sensitivity analyses to assess the robustness of our findings.

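### The Hotelling gate that sets the Aim 1 significance level has no stated facility adjustment, so at the plan's own ICC the promised experimentwise error control is not delivered

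*Supplement*

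**What the plan says.** The plan's aim is explicit in Section 9.3.1: "The two-step protected test approach will be used to control the experimentwise type I error rate from multiple outcomes".

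Section 9.3.2 (Aim 1) gives the steps. A Hotelling test is run first, with this purpose: "simultaneously compare the baseline to follow-up change in the three primary outcomes between the arms to protect the type I error rate from multiplicity". When it is significant, each outcome is then tested with no more adjustment. If it is not, testing still goes ahead: "If not, subsequent comparisons will be performed with a conservative Bonferroni correction", at 0.05/4 = 0.0125. The linear mixed models come second, and the facility random effect is specified for them only.

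Facilities are randomised to the exercise programme (Section 9.1). Section 9.2 assumes an intracluster correlation (ICC) of 0.1 and inflates the sample by a design effect of 1.90.

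The outcomes are counted differently from place to place:
- Section 9.1 lists three measures (LLFDI, 6MWT, gait speed).
- The gate refers to three outcomes, while the Bonferroni divisor is four.
- Table 1 powers four: LLFDI overall function, LLFDI disability frequency, gait speed and 6MWD.
- Section 6.2.1.1 says "We will focus our analyses on the LLFDI function and disability dimension scores" and names five. LLFDI overall function, which Table 1 powers, is not among them.

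**The concern.** The gate decides whether every Aim 1 outcome is judged at 0.05 or at 0.0125. An ordinary two-sample Hotelling test treats participants as independent. When whole facilities are allocated and participants within them are correlated, it underestimates the variance of the arm difference and rejects too often under the null. The plan treats clustering as strong enough to nearly double the sample, yet states no allowance for it in the test that sets the significance level.

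A second weakness remains even with a gate of correct size. Passing it releases all outcomes at 0.05, so one real effect removes the multiplicity protection from the rest.

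**Working it through.** **Inputs from the protocol.** Two-sided alpha 0.05; 280 participants, 140 per arm; class size 10; attrition 10%; ICC 0.1; design effect 1.90 (Section 9.2). At least 28 facilities (Section 12), or about 34 (Section 4). Gait speed: target difference 0.10, SD of change 0.20 (Table 1).

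**Assumptions not in the protocol.** Correlation between outcomes 0, 0.3 or 0.6; the same ICC for each outcome; equal cluster sizes.

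**1. The plan's own figures reproduce.** 0.05/4 = 0.0125. Design effect 1 + (10 − 1) × 0.1 = 1.90. Two-sample t-tests at 80% power need 41, 37, 64 and 13 completers per arm. Multiplying by 1.90/0.90 gives 86.6, 78.1, 135.1 and 27.4, rounded up to 90, 80, 140 and 30, as in Table 1.

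**2. Size of a participant-level gate.** Under the null the statistic is roughly the design effect (DE) times a chi-square on p degrees of freedom, so size ≈ P(χ²ₚ > χ²ₚ,₀.₉₅ / DE).
- DE 1.90 (10 per facility): 7.815/1.90 = 4.11 gives 25% for p = 3; 9.488/1.90 = 4.99 gives 29% for p = 4.
- DE 1 + 8 × 0.1 = 1.80 (9 completers): 23% and 26%.
- DE 1 + 6 × 0.1 = 1.60 (34 facilities; 280/34 × 0.9 ≈ 7 completers): 18% and 20%.

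**3. Whole procedure under the global null.** Simulation, 20,000 replicates per setting, ICC 0.1. The gate is a participant-level Hotelling test at 0.05. Facility-level t-tests, standing in for the mixed models, follow at 0.05 if the gate passes and 0.0125 if it fails. Ranges are over the assumed correlations.

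| Facilities × completers | Outcomes | Gate rejects | At least one false claim |
|---|---|---|---|
| 28 × 9 | 3 | 22–23% | 10–13% |
| 28 × 9 | 4 | 26% | 12–16% |
| 34 × 7 | 3 | 18% | 9–11% |
| 34 × 7 | 4 | 20–21% | 11–15% |

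**4. Other ICC values** (four outcomes, 28 × 9). At correlation 0.3 the false-claim rate is 11% at ICC 0.05 and 7–8% at ICC 0.01–0.02. Over correlations 0–0.6 the ranges are 9–12% and 6–9%.

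**5. Which part does the damage** (28 × 10, ICC 0.1).
- Going on after a failed gate adds 0.02–1.1 percentage points behind the participant-level gate, and about 1–2 points behind a gate on facility means.
- A facility-mean gate with the 0.0125 fallback gives 4.4–5.5% (three outcomes) or 5.3–6.8% (four).
- A facility-mean gate that stops on failure gives 3.4–4.6%.

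**6. One outcome truly improves** (assumed effect 0.65 SD, four outcomes). Behind a facility-mean gate, the chance of a false claim among the other three is 11.6–13.5%. A separate large-sample calculation with a valid gate gave 12.6–14.1%.

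**7. Holm on the clustered p-values, no gate.** About 4–5% under the global null and about 4–5% among the other three outcomes when one improves.

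**8. Power for gait speed.** Effective completers per arm: 140 × 0.9/1.90 = 66.3. Noncentrality: (0.10/0.20) × √(66.3/2) = 2.88. Power is Φ(2.88 − 1.96) ≈ 82% at 0.05 and Φ(2.88 − 2.50) ≈ 65% at 0.0125; the t distribution gives 82% and 64%.

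**The case against.** The best reply is that the protocol never says the gate ignores facilities. It names a Hotelling test and is silent on its unit, while clustering is handled in the randomisation, the sample size, the mixed models and the GEE models. The formal Aim 1 tests are the mixed models, and they carry the facility effect. This stands as a limit on wording: the fault is an unstated adjustment, and the Aim 1 p-values themselves are not naive. It does not rescue the procedure, because the gate still sets the level at which those p-values are read, and a reader programming from the text would run the ordinary test.

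The size also depends on a planning ICC applied equally to every outcome. That is fair, and the excess shrinks at smaller values. It does not vanish: with four outcomes and correlation 0.3 the rate is 6.5% even at ICC 0, because of the 0.0125 fallback.

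The outcome count can be partly read from the text. Three measures become four once LLFDI is split into function and disability as in Table 1, which would explain both the gate and the divisor. That reading is plausible but unwritten, and it does not explain the five dimension scores. Section 6.2.1.1 neither calls those five primary nor rules out the overall score, so a seven-outcome family is not established.

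The protocol also cites precedent for the protected test. It describes no adaptation of that approach to cluster randomisation.

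**Conclusion.** The point holds and should be settled before any unblinded analysis. Run on participants at ICC 0.1, the two-step rule gives a false-claim rate of roughly two to three times 5%. The main cause is the missing facility adjustment in the gate. Adding that adjustment alone would leave only weak control, as step 6 shows. The figures rest on the assumed correlations, equal ICCs and equal cluster sizes.

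Three stronger readings are tempting and unsupported:
- *The mismatch between three and four outcomes inflates error.* It does not by itself: 0.0125 is stricter than 0.05/3 = 0.0167. It is an inconsistency that leaves the Hotelling vector undefined.
- *Testing on after a failed gate is what breaks control.* It adds almost nothing behind the liberal gate. Behind a valid one it adds 1–2 points, and three highly correlated outcomes then stay under 5% (4.4%).
- *The primary effect tests ignore clustering.* They do not; the mixed models include facility.

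**What to change.** - State one primary family, the same in Section 6.2.1.1, Table 1 and Section 9.3.2. The four Table 1 outcomes would fit the existing divisor; the choice is the sponsor's. Say what status the remaining LLFDI scores have.
- Drop the Hotelling gate and apply Holm to the primary p-values from the mixed models with a facility random effect.
- If a global test is still wanted, keep it as descriptive. Run it on facility mean changes, or in a joint mixed model, with degrees of freedom based on facilities.

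The cost is protocol wording and a few lines of code, with no new data. Gait speed, the outcome that drives the 140 per arm, keeps about 82% power if it is tested at 0.05 but about 64% if it must meet Holm's first step at 0.0125. The statement of at least 80% power for all main outcomes should be qualified for it.

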## 9 STATISTICAL CONSIDERATIONS

### 9.1 General Design Issues

A randomized trial is needed to control for confounding factors that affect the outcome. There are no ethical issues regarding a randomized trial since both groups will be receiving an active exercise intervention delivered by trained personnel. We carefully considered the advantages and disadvantages of randomizing at the level of the facility and the resident. Given the amount of interaction that occurs between subjects within a facility, it is imperative that we conduct a cluster randomized trial, and randomize by facility to exercise programs. If we randomize at the resident, participants would discuss details of their intervention and cause cross-contamination between the intervention arms. Unlike a traditional trial in which participants are randomized as they are being recruited, a cluster randomized trial also affords the additional benefit of examining the facility characteristics such as type (independent living/senior high rise) and size, and ensuring a balance in those characteristics is achieved by design rather than chance. Once the facilities are randomized to exercise program, we will then randomize within facility for delivery mode (i.e. subjects will be randomized to either an exercise leader or staff activity person led exercise program). Randomization for delivery mode will occur after baseline testing. We will use a commercially available high quality pseudo-random deviate generator such as that available in SAS® (SAS Institute, Inc., Cary, North Carolina) known to be free of serial correlations(56) to randomize facilities to the two arms in a 1:1 ratio, stratified by facility type. In addition, the proposed design reaps the advantages of a paired comparison for the exploratory hypothesis (Aim 2) as both exercise leaders and staff activity personnel will be delivering On the Move in the same set of facilities, where feasible to train a staff person ready to lead the class safely and per protocol.

The main outcomes are self-reported function and disability (Late Life Function and Disability Index/LLFDI) and walking ability (6-minute walk test/6MWT and gait speed). We will also examine satisfaction, attendance rates and adverse event (falls, soft tissue injuries, muscle soreness, etc) rates.

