| LLFDI Disability Frequency | 6.35                             | 4.76                            | 3.18 ( $d=0.5$ )                        | 37                                                      | 80                              |
| Gait Speed (m/s)           | 0.13                             | 0.20                            | 0.10                       | 64                                                      | 140                             |
| 6MWD (m)                   | 62.0                             | 42.8                            | 50                         | 13                                                      | 30                              |

Our sustainability Aim 2 depends on whether we are able to train a staff activity person ready to lead a class safely and per protocol. Further, we do not have a priori data in sufficient detail that allows us to reliably estimate the likelihood of suitably training a staff activity person in each of the main type of facility. Thus Aim 2 is exploratory in nature and we will also focus on barriers to suitably training a staff activity person. We anticipate that we will enroll approximately 120 participants into Aim 2. The power available to detect a statistically significant difference in gains attributable to *On the Move* when delivered by exercise leaders and staff activity personnel (sustainability hypothesis – Aim 2) are in **Table 4**. Power is  $\geq 90\%$  for all outcomes except for gait speed when comparing *On the Move* to Standard when delivered by facility staff in which case power is 78%.

1029 **Table 4. Number needed to enroll for establishing sustainability of *On the Move*, incorporating clustered design**  
 1030 **(x0.90), attrition (10%), and rounded up to class size of 10.**

| Outcome                    | Prior Information                |                                 |                                         | Estimated Sample Size                                      |                                 | New Aim 2 Statistical Power with Anticipated N=140+140+60+60                |                                                                                       |

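### The Aim 1 model omits facility type, the stratification factor, and sections 9.3.1 and 9.3.2 disagree on whether significance-selected covariates enter the primary analysis

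*Supplement*

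**What the plan says.** All references are to protocol version 2.0 (12/03/2015).

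- **Randomisation (section 9.1).** A pseudo-random generator will be used "to randomize facilities to the two arms in a 1:1 ratio, stratified by facility type". The same section gives balance on facility characteristics, secured by design, as a benefit of randomising clusters.
- **Aim 1 model (section 9.3.2).** Change from baseline is modelled with intervention arm as the effect of interest, "baseline value of outcome as an additional fixed effect covariate; and a facility random effect". Facility type is not listed.
- **Covariates, Overview (section 9.3.1).** Baseline characteristics are compared between arms, and "any significant differences will be noted and accounted for as covariates in the main analyses". The main analyses are said there to cover Aims 1 to 3.
- **Covariates, Aim 1 (section 9.3.2).** "We will consider adding other baseline measures found to be significantly" different between the arms, or judged important, but with the stated purpose of checking robustness.
- **Covariates, Aims 2 and 3 (sections 9.3.2 and 9.3.3).** The Aim 2 mixed model and the Aim 3(a) and 3(b) GEE models place measures found to differ between arms in the model itself. None of them names facility type.

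**The concern.** There are two separate issues.

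First, stratified allocation balances facility type across the arms, which lowers the true sampling variance of the treatment effect if type predicts change. A model without type does not credit this. The facility random effect handles the correlation within facilities, but it leaves differences between types in the error against which the arms are compared. The interval is then wider than it needs to be and the test runs below its nominal level.

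Second, two analysts could both follow the plan and fit different primary models for Aim 1. One, reading section 9.3.1, would add every baseline measure that happened to differ significantly. The other, reading section 9.3.2, would adjust only for the baseline value of the outcome. Under randomisation a significant baseline difference arises by chance and says nothing about whether the measure is prognostic. The first reading therefore makes the confirmatory model depend on the data without targeting precision.

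**Working it through.** **Reproducing the plan's figure.** Section 9.2 uses "two-tailed tests conducted at the" 0.05 level, ICC 0.1, a design effect of 1 + (10 − 1) × 0.1 = 1.90, and 10% attrition. Gait speed drives the size; its row in Table 1 reads "Gait Speed (m/s) | 0.13 | 0.20 | 0.10 65 | 64 | 140" (the 65 is a citation mark).

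- Two-sample t-test, difference 0.10, SD 0.20, 80% power: 64 completers per arm.
- 64 × 1.90 / 0.90 = 135.1, rounded up to 140.
- The other three rows also reproduce (41, 37 and 13 completers; 90, 80 and 30 enrolled).
- Power for gait speed at 140 per arm: 140 × 0.9 / 1.9 = 66.3 effective completers, about 82%.

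So "a total of 280 participants with 140 in each arm" agrees with the plan's inputs.

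**Effect of omitting type.** Section 4 anticipates about 34 facilities (10 independent living facilities, about 24 senior housing sites). Completers per facility: 280 / 34 × 0.9 = 7.41. Between-facility variance: 0.1 × 0.20² = 0.004. Within-facility variance: 0.036. Let s be the share of between-facility variance explained by type. This share is an assumption; the documents give no figure. With type balanced across arms, the true variance of the arm difference is

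Var = [(1 − s) × 0.004 + 0.036 / 7.41] × 4 / 34

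- s = 0: SE 0.0323 m/s
- s = 0.25: SE 0.0304 m/s
- s = 0.50: SE 0.0284 m/s

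A model without type keeps reporting about 0.032 whatever the value of s. A model with type reports the smaller figure. For s = 0.50 the ratio is √(0.008857 / 0.006857) = 1.14.

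A simulation (40,000 runs per setting; 1:1 within type; analysis of facility means, which equals the random-intercept model when facilities are of equal size) gave for gait speed, 34 facilities:

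| Share explained by type | 95% CI half-width without / with type (m/s) | Ratio | Power without / with | Type I error without type |
|---|---|---|---|---|
| 0% | 0.0653 / 0.0654 | 1.00 | 85% / 85% | 4.9% |
| 25% | 0.0654 / 0.0615 | 1.06 | 86% / 89% | 3.8% |
| 50% | 0.0657 / 0.0574 | 1.14 | 88% / 93% | 2.5% |

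With type in the model, type I error was about 5% throughout. With 28 facilities (an assumed mix of 8 and 20), the ratios were 1.00, 1.07 and 1.17; power was 81, 83 and 84% without type and 81, 86 and 91% with it.

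**Selecting covariates by significance.** The plan gives neither the level nor the number of baseline tests. Assuming independent tests at 5%, the chance of at least one significant difference under sound randomisation is 1 − 0.95^k: 23% for k = 5, 40% for k = 10 and 54% for k = 15. On the section 9.3.1 reading, a chance-selected covariate entering the primary model would thus be common.

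**The case against.** **The Aim 1 text already fixes the covariate.** A reader might infer that the Aim 1 model is built on baseline significance tests. The text does not support that: section 9.3.2 names the baseline value of the outcome and keeps other measures for robustness. This part stands. The fault for Aim 1 is the conflict with section 9.3.1, which may be a leftover sentence but is current text.

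**The loss of precision is conditional.** It is zero if type does not predict 12-week change. This also stands, and the result can only be given as a range.

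**The power gain is easily overstated.** A reader might take 28 facilities with 9 completers each and hold the unadjusted normal-approximation power at 84% (SE 0.0338), against 89 to 93% with type in the model. That treats stratification as if it had not already reduced the true variance, ignores the limited facility degrees of freedom, and uses 28 facilities where version 2.0 anticipates about 34. Like for like at 34 facilities and 25 to 50% explained, the gain is 3 to 5 points.

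**The GEE models are a different matter.** They have no facility variance component, and adding a covariate to a logit model changes the odds ratio being estimated. Section 7.1 expects falls and cardiac events in under 1% of people, fewer than 280 × 0.01 = 2.8 participants, so extra terms may not be estimable. This stands for rare events.

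**A final covariate list could sit in a separate analysis plan.** None is shown, so the absence of a longer list is not held against the protocol. But section 9.3.2 does write out the Aim 1 model, and the contradiction lies within section 9.3 itself.

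**Conclusion.** Both narrow points hold. The stratification factor is missing from the written Aim 1 model, and the primary covariate set is not uniquely fixed.

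The cost of the first is moderate and uncertain. At ICC 0.1 with about 34 equal-sized facilities, the interval is 0 to 14% wider and power 0 to 5 points lower if type explains 0 to 50% of between-facility variance. Section 4 says numbers per site will vary, so these figures are approximate.

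A reader might infer that the trial is underpowered or its test invalid. Neither follows. Omitting type causes no bias and does not inflate type I error, and in every setting examined power stays above the promise to detect statistical "significance in intervention effects in all main outcomes with at least 80% statistical power". The sample size need not change.

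The cost of the second is loss of prespecification. On one of two permitted readings, chance imbalance decides what is in the confirmatory model. This should be corrected, but it does not undermine the design.

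**What to change.** 1. Add facility type as a fixed effect in the Aim 1 and Aim 2 linear mixed models, coded with the strata actually used at randomisation. Define those strata first: section 9.1 gives independent living and senior high rise as types, while sections 3 and 4 also admit community centers, and the projected 34 sites in section 4 count none.
2. Delete the rule in section 9.3.1 that significant baseline differences enter the main analyses, and the matching wording in the Aim 2, 3(a) and 3(b) models.
3. Keep any further covariates to a short list, fixed in advance, from data already collected (for example age and sex).
4. In the Aim 3 GEE models, include type only where event counts allow.

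The cost is a change of wording and one or two between-facility degrees of freedom out of about 32 (34 facilities less two for intercept and arm). No new data are needed.
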